| **Primary registry and trial identifying number** Pan African Clinical Trial Registry  PACTR202109586388973  **Date of registration in primary registry** 28 September, 2021  **Secondary identifying numbers/Acronym** I-decide  **Source(s) of monetary or material support:** The PI ([name])  **Primary sponsor**: The PI  **Secondary sponsor(s)**: None  **Contact for public queries**: [name], BScN, MScN [[name]] [[contact]]  **Contact for scientific queries**: [name], BScN, MScN [[name]] [[contact]]  **Public title**: Effectiveness of targeted antenatal family planning information provision on early postpartum family planning uptake in Kisumu county  **Scientific title:** Targeted Antenatal Information Provision and Postpartum Fertility Decisions  **Countries of recruitment**: Kenya  **Health condition(s) or problem(s) studied**: Female Fertility, Contraceptives  **Intervention(s)**  **Active comparator:** Antenatal provision of Postpartum Family Planning (PPFP) Information and appointment setting for 14 weeks postpartum follow-up  **Control comparator:** Routine Antenatal care  **Key inclusion and exclusion criteria** The study will be conducted in 4 primary health centres and 2 communities in the Kisumu East sub-county. The Health centres are eligible if : They offer the continuum of ANC, delivery, and PNC; They provide a selection of at least three modern contraceptive methods that are rated 2 or 1 on the Medical Eligibility Criteria (MEC) for Postpartum Contraceptives and referrals for other methods to clients; There were no stock-outs of contraceptives during the preceding six months; They have on average at least 10 deliveries per month; and They are willing to participate.  All pregnant women will be eligible to participate in the study if: They are in their second pregnancy trimester; The woman is attending ANC and has intention of attending PNC at the health centre; An informed consent is obtained; and Resides within 20km  Excluded from the study will be clients: in similar study; with latex sensitivity; not anticipating a male partner in the next 12 months; unable to complete consent form as determined by the study nurse or cha and whose only male partner has had a vasectomy.  **Study type** Interventional  **Allocation:** randomized  **Intervention model:** concurrent assignment  **Masking:** None  **Primary purpose:** prevention  Phase II  **Date of first enrolment** Nov 2021  **Target sample size** 246  **Recruitment status** Not Recruiting  **Primary outcome(s)** Nature of Fertility decisions postpartum. Primarily the uptake of immediate postpartum FP being the main outcome – 14 weeks postpartum  **Key secondary outcomes** Fertility intentions. Primarily whether they accept to book an appointment for postpartum family planning - 14 weeks postpartum  Knowledge of family planning methods – Any time after intervention |

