| Outcomes (12) | Primary Outcome  Nature of Fertility decisions postpartum. Primarily the uptake of immediate postpartum FP being the main outcome. To be measured at or after 14 weeks postpartum. It is a proportion.  Secondary Outcome  1. Fertility intentions. Primarily whether they accept to book an appointment for postpartum family planning. Will be assessed soon after the intervention has been administered. It will be a proportion of those intending to use PPFP versus those who participated.  2. Knowledge of family planning methods. Will be assessed soon after the intervention has been administered or recruitment (for controls). It will be a proportion of level of knowledge on PPFP among participated.  3. Uptake of postnatal services. Will be measured at 14 weeks postpartum and it will be a proportion of utilization of postnatal services among participants.  4. Perceived control of fertility decision. Will be a proportion among participants. To be measured soon after intervention or recruitment (for the controls)  5. Attitude toward PPFP Will be a proportion among participants. To be measured soon after intervention or recruitment (for the controls)  No harm outcomes are premeditated |
| Participant timeline (13) | This being a behavioural intervention, the recruitment and interventions will be done simultaneously.  Client exit interviews will be done immediately or soonest possible time after the intervention  Questionnaire will be administered at or soon after 14 weeks postpartum.  (see annexes 1 and 2)  [figure not shown] |

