| Recruitment (15) | Each health centre and community unit will have a trained research assistant. The assistant is to ensure adherence to the study manual and standard operating procedures for data management. The primary outcomes will largely be assessed based on the CRFs, appointment card and questionnaire. Actual uptake of modern contraceptive method will be established three months postpartum between the 12th to 14th weeks after birth. The CRFs will be filled on recruitment by the trained ANC service provider. The appointment card will be filled by the health worker after the client has accepted to set postnatal follow up date for PPFP. The questionnaire will be filled at 14 weeks postpartum during the scheduled MCH visit by a trained enumerator.  The client exit interview guide and site visit appraisal form will be used to assess the process indicators. Client exit interviews will be done by trained enumerator on the earliest opportunity after the intervention has been administered to reduce recall bias by the client. Site appraisal form will be filled on site visits by the research team and on the part of enumerator will be filled each day to include workload for ANC, number of staff available to offer ANC services, availability of FP counselling bag and flipchart. Lose to follow-up will be called to find the status of the client |
| **Methods: Assignment of interventions (for controlled trials)** | |
| Allocation: |  |
| Sequence generation (16a) | Each client meeting the criteria will be randomly assigned to the study i.e. to the intervention and to the control arms using simple random sampling by picking folded paper labelled “yes” or “no”. There will be no blinding as the intervention facilities and controls are known and will be separate to reduce contamination. |
| Allocation concealment mechanism (16b) | There will be no allocation concealment as the intervention and control facilities are known and separate to reduce contamination. |
| Implementation (16c) | The allocation to intervention and control is at the facility level. The participants will be enrolled by the study nurse for both the community and facility arms. Participants will be assigned to participate by picking a ballot paper labelled “yes” or “no” enclosed in resembling envelopes |
| Blinding (masking) (17a,b) | None of the implementers and participants will be blinded thud there equally no plan for controlled unblinding. |

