| **Methods: Data collection, management, and analysis** | |
| Data collection methods (18a,b) | Each health centre and community unit will have a trained research assistant. The assistant is to ensure adherence to the study manual and standard operating procedures for data management. The primary outcomes are; PPFP knowledge, the intent for use of PPFP (behavioural contracting) and the actual uptake of modern contraceptive methods at three months postpartum will largely be assessed based on the CRFs, appointment card and questionnaire. Actual uptake of modern contraceptive method will be established three months postpartum between the 12th to 14th weeks after birth. The CRFs will be filled on recruitment by the trained ANC service provider. The appointment card will be filled by the health worker after the client has accepted to set postnatal follow up date for PPFP. The questionnaire will be filled at 14 weeks postpartum during the scheduled MCH visit by a trained enumerator.  A process evaluation will be undertaken with the objectives of understanding the barriers and enablers related to the delivery of PPFP. This will be evaluated based on client exit interviews and site appraisal forms. The client exit interview guide and site visit appraisal form will be used to assess the process quality indicators which will include: waiting time, time/trimester of start of FP counselling, time after FP counselling, group/ individual session, availability of teaching aid on the table during counselling, gauging FP information level, application of GATHER (Greet, Ask, Tell, Help, Explain and Return/Refer) Model and BRAIDED (Benefits, Risks, Alternatives, Inquiries, Decision, Explanation, Documentation) Model. Satisfaction with information given, responses to questions, respectful care, confidentiality and privacy. Client exit interviews will be done by trained enumerator immediately after the intervention has been administered to reduce recall bias by the client. Site appraisal form will be filled on site visits by the research team and on the part of enumerator will be filled each day to include workload for ANC, number of staff available to offer ANC services, availability of FP counselling bag and flipchart. |

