| Participant retention and complete follow-up will be promoted by ensuring that, first, the intervention and follow up are not so far apart and the there is no none routine appointment i.e. the follow-up appointment is set on the second immunization and postpartum care visit. Secondly, part of the inclusion criteria is distance of not more than 20 Km thus increasing access. Third is that the data collection forms have been converted to Kobo tool box with strict skip logics and restrains for required data. This is to ensure completeness of the data.  Diary of the return date of 14 weeks postpartum will be kept with telephone number to call the client up to 2 days after the material date |

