| There are no additional methods proposed in this protocols. Any amendments will be communicated. |
| Intention to treat will be applied to protocol non-adherence.  Automatic linear model regression multiple imputation with 5 iterations with history for comparison of variance will be applied in handling of missing values. |
| **Methods: Monitoring** | |
| Data monitoring (21a,b) | Data management team will comprise the PI, Data Clerks at the sites and the study nurse and Community Health Worker: set acceptance rate proportion (those who accepted to participate versus those sampled), monitoring retention (percentage of participants proceeding from recruitment, treatment to follow-up including missing outcome data), monthly forecast of recruitment for the trial period remaining, monitoring loss to follow-up as a proportion of the ones not yet reached by 16 weeks postpartum follow-up to those who were recruited, overseeing data management metrics i.e. rate of electronic data capture, return dates and rate of returns, number of completed follow-up, withdrawal rate, monitoring intervention fidelity by the study nurse or Community Health Worker (CHW), Data quality checks, results dashboard review |
| The interim analysis will be for monitoring purposes from the Kobo toolbox dashboard. It will be used to determine acceptance rate and retention rate and forecasting trial period remaining and the proportion of the unreached or dropout rate. This being a behavioural intervention study, the researcher did not envisage a circumstance warranting prior termination of the trial due to internal factors. |
| Harms (22) | The study doesn’t envisage adverse events as it is a behavioural interventional study seeking to augment a vital preventive service. |
| Auditing (23) | The trial will be audited on monthly basis. The core and site trial team plus the facility in-charge and Sub-county RH coordinator will be involved in the auditing. |
| Ethics and dissemination | |
| Research ethics approval (24) | The study has undergone ethics review by Masinde Muliro University of Science and Technology (MMUST), (MMUST/IERC/013/2021) and has been licensed by the National Commission for Science, Technology and Innovation (NACOSTI), Ref. No. 522628. Informed consent will be sought before participant can be recruited |

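### Secondary outcome 3 (uptake of postnatal services) is recorded at a postnatal visit with no rule for women who miss it, so it risks a ceiling and selection on attendance

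*Protocol*

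**What the plan says.** Outcomes (12) defines secondary outcome 3 as: "Uptake of postnatal services. Will be measured at 14 weeks postpartum and it will be a proportion of utilization of postnatal services among participants". It names no particular service, minimum number of contacts or time window.

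Recruitment (15), Data collection methods (18a,b) and Data management (19) all state where the 14-week data are collected: "The questionnaire will be filled at 14 weeks postpartum during the scheduled MCH visit by a trained enumerator". The retention paragraph under Data collection methods explains that no extra appointment is created, because "the follow-up appointment is set on the second immunization and postpartum care visit". Participant timeline (13) gives the time but no place: "Questionnaire will be administered at or soon after 14 weeks postpartum".

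For women who do not return, Recruitment (15) says: "Lose to follow-up will be called to find the status of the client". The retention paragraph adds a diary of return dates with a "telephone number to call the client up to 2 days after the material date". Statistical methods (20a,b,c) specifies intention to treat, and says that multiple imputation "will be applied in handling of missing values", with no exception for this outcome.

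The inclusion criteria in the registry summary at the front require: "The woman is attending ANC and has intention of attending PNC at the health centre". Eligibility criteria (10) does not repeat this. Under Interventions (11), setting a postpartum appointment belongs to the intervention, and controls receive routine antenatal care.

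**The concern.** The place of measurement is itself an instance of the thing measured. A woman who completes the questionnaire at a postpartum care visit has, on the widest reading of the definition, used a postnatal service. The women most likely to be non-users are those who do not come, and the protocol does not say how they are classified. For this outcome, being observed and having the outcome nearly coincide, so missingness is informative.

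This can affect the comparison between arms as well as the level. Appointment setting is meant to bring women to the 14-week visit. If it works, the control arm has more non-attenders, so more of its non-users go unrecorded or are imputed as users. A real benefit on postnatal care would then be reported as smaller than it is.

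**Working it through.** **The plan's own figures.** The protocol gives no expected rate or power for this outcome, so there is no stated figure to reproduce. The only number needed is the arm size. Sample size (14) gives 246 women at 41 per site; with two sites per arm that is 82 per arm (3 × 82 = 246). This was set for the primary outcome at 27% against 53%. The printed formula gives 73 per arm, and with a continuity correction 81 per arm (243 in total), close to the stated 246. The sample size is not in dispute here.

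**Inputs for the illustration (assumed, because the documents give none).**
- a: true proportion attending the 14-week visit. Uptake is read as attending that visit, so attenders are users and non-attenders are non-users.
- r: share of non-attenders whose status on this outcome is obtained by telephone, taken as equal in the two arms.

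**Formula.** Of all enrolled women in an arm, a are recorded as users, r(1 − a) are recorded as non-users, and (1 − r)(1 − a) have no data. The observed proportion is

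a / [a + r(1 − a)].

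Imputing within an arm from the women who have data gives back about this same proportion, so it does not restore the missing non-users.

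**Worked case, 60% against 80%.**
- r = 0: 0.60/0.60 = 100% and 0.80/0.80 = 100%; difference 0.
- r = 0.25: 0.60/(0.60 + 0.10) = 85.7% and 0.80/(0.80 + 0.05) = 94.1%; difference 8.4 points.
- r = 0.5: 0.60/(0.60 + 0.20) = 75.0% and 0.80/(0.80 + 0.10) = 88.9%; difference 13.9 points.
- r = 0.75: 0.60/(0.60 + 0.30) = 66.7% and 0.80/(0.80 + 0.15) = 84.2%; difference 17.5 points.
- r = 1: 60% and 80%; difference 20 points.

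Starting from 82 per arm, with only the women who have data, two-sided 5% power is about 36% at r = 0.25, 57% at r = 0.5, 71% at r = 0.75 and 80% at r = 1. These figures ignore clustering.

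**Range over other assumed rates (observed difference in points).**

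| True rates | r = 0 | r = 0.25 | r = 0.5 | r = 1 |
|---|---|---|---|---|
| 50% vs 70% | 0 | 10.3 | 15.7 | 20 |
| 60% vs 80% | 0 | 8.4 | 13.9 | 20 |
| 70% vs 90% | 0 | 7.0 | 12.4 | 20 |
| 70% vs 80% | 0 | 3.8 | 6.5 | 10 |

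**When dilution is assured.** With equal r, the observed difference is the true difference times r / {[a₁ + r(1 − a₁)][a₂ + r(1 − a₂)]}. If at least half attend in each arm, each bracket is at least (1 + r)/2, and [(1 + r)/2]² is never below r, so the multiplier cannot exceed 1. With unequal r the result can move either way. In the 60% against 80% case, reaching a quarter of control and half of intervention non-attenders gives 88.9 − 85.7 = 3.2 points; the reverse gives 94.1 − 75.0 = 19.1 points.

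**The case against.** A reader might infer that non-attenders are treated as missing, that the outcome is therefore near 100% in every arm by construction, and that it cannot show an effect. The documents do not support this. No section says that a missed visit becomes a missing value. Those lost are to be telephoned, Data monitoring (21a,b) counts loss as not being reached by 16 weeks, the denominator is participants, and analysis is by intention to treat. The full ceiling needs two conditions that the protocol does not state: that the calls yield nothing on this outcome, and that the study visit itself counts as use. If the calls yield something, a difference survives. If the outcome means earlier contacts or particular services, attenders can differ too.

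That limits the claim but does not remove the problem. The stated purpose of the call is to learn the client's status, and nothing says that it records postnatal service use. The denominator and intention to treat fix who is counted, not how a woman who missed the visit is scored. An analysis plan may add a missing-data rule, but it cannot supply data that the sites were never asked to collect.

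A reader might also blame the ceiling on enrolling women who intend to attend postnatal care. That criterion appears only in the registry summary, applies to all arms and does not ensure attendance. It limits generalisability and does not create the ceiling.

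Two further points stand. This is one of five secondary outcomes, and it is absent from the registry summary's key secondary outcomes and from the objectives. Also, scoring women without a site record as non-users can misclassify care received elsewhere, possibly to a different extent by arm.

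**Conclusion.** The concern holds as a risk of a ceiling and of selection on attendance, not as a certainty. As written, the outcome is collected at a visit that can itself satisfy it, women who miss the visit have no stated classification, and the general imputation rule would move non-users toward use.

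The likely consequence is dilution of any true difference. For an assumed true 60% against 80%, the 20 points become about 8 if a quarter of non-attenders are reached, about 14 if half are, and 0 if none are. This rests on assumed attendance and reach, on counting the study visit as use, and on equal reach in both arms. Unequal reach makes the direction uncertain. The point should be fixed, but it concerns a secondary outcome and leaves the primary comparison untouched.

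**What to change.** In Outcomes (12), define secondary outcome 3 as at least one postnatal care contact before the 14-week study visit, so that the study visit does not count. Ascertain it for every enrolled woman from the site's postnatal and immunisation records, and use the planned call to ask about contacts, including those at other facilities.

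In Statistical methods (20c), classify women with no contact by record or call as non-users, rather than imputing them from attenders. Add a sensitivity analysis that treats women with no record and no completed call as missing. If the registry's intention criterion is kept, state that the result applies to women who intended at enrolment to attend postnatal care.

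The cost is a small register check by the research assistants already planned for each health centre and community unit, an added question in the call, and a few lines of text. The downside is that care at non-study facilities may be missed when the call fails; the sensitivity analysis shows how much depends on those women.

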| Data management (19) | **Data collection Procedure**  Five tools will be used for data collection, namely; client exit interview guide, case report form, appointment card, Site appraisal form and questionnaire. All the tools will be used to collect quantitative data except site appraisal form and some questions in the questionnaire that need brief explanation. The theory of planned behaviour was applied to design quantitative process and outcome indicators and thus the tools (Ajzen & Klobas, 2013). Client exit interview guide and Site appraisal form will be developed based on the procedures set out in the counselling guide. Appointment card will be source of information on client details, proposed date for PPFP initiation and vital PPFP information summary.  **Data collection**  Each health centre and community unit will have a trained research assistant. The assistant is to ensure adherence to the study manual and standard operating procedures for data management. The primary outcomes are; PPFP knowledge, the intent for use of PPFP (behavioural contracting) and the actual uptake of modern contraceptive methods at three months postpartum will largely be assessed based on the CRFs, appointment card and questionnaire. Actual uptake of modern contraceptive method will be established three months postpartum between the 12th to 14th weeks after birth. The CRFs will be filled on recruitment by the trained ANC service provider. The appointment card will be filled by the health worker after the client has accepted to set postnatal follow up date for PPFP. The questionnaire will be filled at 14 weeks postpartum during the scheduled MCH visit by a trained enumerator.  A process evaluation will be undertaken with the objectives of understanding the barriers and enablers related to the delivery of PPFP. This will be evaluated based on client exit interviews and site appraisal forms. The client exit interview guide and site visit appraisal form will be used to assess the process quality indicators which will include: waiting time, time/trimester of start of FP counselling, time after FP counselling, group/ individual session, availability of teaching aid on the table during counselling, gauging FP information level, application of GATHER (Greet, Ask, Tell, Help, Explain and Return/Refer) Model and BRAIDED (Benefits, Risks, Alternatives, Inquiries, Decision, Explanation, Documentation) Model. Satisfaction with information given, responses to questions, respectful care, confidentiality and privacy. Client exit interviews will be done by trained enumerator immediately after the intervention has been administered to reduce recall bias by the client. Site appraisal form will be filled on site visits by the research team and on the part of enumerator will be filled each day to include workload for ANC, number of staff available to offer ANC services, availability of FP counselling bag and flipchart.  Internal consistency will be ensured by piloting the tools and refining them to ensure they capture the essence of what they were meant to collect and Cronbach’s alpha of 0.7 will be acceptable. |

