| Statistical methods (20a,b,c) | Quantitative data entry will be done in IBM’s SPSS version 26. The sub-Country research teams will be responsible for verifying the data and a second verification will be done by the researcher to monitor data quality. Questions about data inconsistencies or missing values will be sent to sites and will be resolved on an ongoing basis. The participant will form the unit of analysis and intra-cluster correlation coefficient will be accounted for. All analysis will be by intention to treat Descriptive statistics will be performed by computing means, standard deviations, and minimum and maximum values for continuous variables, and frequencies and percentages for categorical variables. As part of quality control and descriptive analysis of the data, the distribution of variables to detect outliers will be examined. Descriptive statistics will be tabulated for individual clusters and aggregated across clusters.  On evaluating the effect of socio-cultural beliefs on Postpartum Family Planning uptake among postpartum mothers in Kisumu County, descriptive statistics on of prevalent sociocultural beliefs about PPFP will be summarized into frequencies and percentages. Bivariate analysis of effects of sociocultural beliefs on PPFP uptake will be done and presented on two-by-two (2x2) tables with Chi-square being the inferential statistics where P-value will determine the significance of homogeneity of proportions and odds ratio (OR) and 95% confidence interval (95% CI) will demonstrate the strength of the relationship. Binary logistic regression analysis will be done to adjust for confounders of sociocultural beliefs as determinants of PPFP uptake  Perceived individual control of Postpartum Family Planning choice among postpartum mothers in Kisumu County will be analysed using descriptive statistics aggregated based on sociodemographic aspects and presented in tables with means, median, range and standard deviation. This will further be analysed by student t-test to ascertain the significance in differences in means for the determinants of perceived control of family planning choice Significant determinants will be fitted in multilinear regression analysis to adjust for confounders  Fertility intentions for postpartum mothers will be disaggregated based on sociodemographic aspects and other individual characteristics. Intention to use PPFP will be simplified in proportions of the categorical yes or no to appointment for PPFP. Bivariate analysis of determinants of fertility intentions will be done and presented in two-by-two (2x2) tables with Chi-square being the inferential statistics. Binary logistic regression analysis will be done to adjust for confounders of determinants of fertility intentions.  Likewise, level of intention will be measure by Likert scale and analysed by t-test statistics after normality testing and adjusted for in linear regression analysis.  Postpartum Family Planning uptake between control and intervention groups of will be compared by use of simple clinical superiority in the proportions.  Bivariate analysis with chi-square statistics will be used to analyse the determinants of Postpartum Family Planning uptake between control and intervention groups and thus will form the selection criteria for inclusion in final regression model. Binary logistic regression analysis will be applied to adjust for confounders |

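### Attitude and knowledge are defined only as proportions, although the tools appear to give graded scores and two sister constructs are analysed as scores; if so, power would be lost

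*Protocol*

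**What the plan says.** Under Outcomes (12), secondary outcome 5 reads "Attitude toward PPFP Will be a proportion among participants" and secondary outcome 2 reads "It will be a proportion of level of knowledge on PPFP among participated". Secondary outcome 4 has the same form: "Perceived control of fertility decision. Will be a proportion among participants". Fertility intention, secondary outcome 1, is also given as a proportion.

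On the tools, Data management (19) states that "The theory of planned behaviour was applied to design quantitative process and outcome indicators and thus the tools", and that after piloting a "Cronbach’s alpha of 0.7 will be acceptable". The alpha criterion is not tied to a named construct.

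Statistical methods (20a,b,c) treats these four outcomes differently:
- Perceived control is "presented in tables with means, median, range and standard deviation", followed by a t-test and multiple linear regression.
- Intention is analysed as yes or no to an appointment, and in addition "level of intention will be measure by Likert scale and analysed by t-test statistics after normality testing", with linear regression after that.
- Attitude and knowledge are given no analysis of their own, either as a proportion or as a score.

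Sample size (14) gives 246 women in total, 41 per site. With three arms of two sites each, that is 82 per arm. No effect size, SD or power target is given for any secondary outcome.

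**The concern.** An information intervention acts first on what women know and how they regard postpartum contraception, so these two outcomes bear directly on whether it worked as intended. Data collection methods (18a,b) and Data management (19) even list knowledge among the primary outcomes, although Outcomes (12) makes it secondary.

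A proportion among participants normally requires each woman to be classed as in or out. If the instrument yields a graded score, that classification discards information already collected, makes the result depend on where the line is drawn, and raises the chance of missing a real difference. The protocol appears to recognise the value of the score for intention and perceived control but does not carry it over to attitude and knowledge.

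**Working it through.** **Step 1: the four outcomes side by side.**

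| Construct | Outcomes (12) | Statistical methods (20a,b,c) |
|---|---|---|
| Intention | proportion | yes/no, and Likert level by t-test and linear regression |
| Perceived control | proportion | means and SD, t-test, linear regression |
| Attitude | proportion | none stated |
| Knowledge | proportion (of level) | none stated |

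An internal-consistency coefficient is a property of multi-item scores, and Outcomes (12) itself speaks of a level of knowledge. Graded measurement is therefore likely for attitude and knowledge, but not documented.

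**Step 2: the protocol's own sample size.** Inputs from Sample size (14): 27% against 53%, two-sided α = 0.05, 90% power, 1:1. With p̄ = 0.40, the printed formula gives

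n = [1.96·√(2·0.40·0.60) + 1.2816·√(0.27·0.73 + 0.53·0.47)]² / 0.26² = 72.5, so 73 per arm (219 in total).

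The usual continuity correction raises this to 80.02, so 81 per arm. Rounding up to an even number for two sites gives 82, and 3 × 82 = 246, the stated total. The 82 per arm is used below.

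**Step 3: score against proportion, ignoring clustering.** Assumptions: a normal score and a standardised difference d, neither given in the protocol. Score: two-sample t-test with noncentrality d·√(82/2). Proportion: the protocol's formula solved for power, with the cut midway between the arm means, so p = Φ(−d/2) and Φ(d/2).

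| d (assumed) | Score | Central cut | Loss (points) |
|---|---|---|---|
| 0.3 | 48% | 33% | 15 |
| 0.4 | 72% | 53% | 19 |
| 0.44 | 80% | 61% | 19 |
| 0.5 | 89% | 72% | 17 |
| 0.6 | 97% | 86% | 11 |
| 0.7 | 99% | 95% | 5 |
| 0.8 | 99.9% | 98% | under 2 |

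A cut at the control median gives 60% at d = 0.44 (50% against Φ(0.44) = 67%), a loss of 20 points. If the uptake contrast of 27% against 53% is borrowed, the implied d is Φ⁻¹(0.53) − Φ⁻¹(0.27) = 0.69, and power is 93% against 99%. That contrast belongs to the uptake outcome and serves only as a reference point.

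Off-centre cuts cost more. At d = 0.44, a cut that 20% of controls exceed gives 55%, and one that 80% of controls exceed gives 43%, against 80% for the score.

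**Step 4: with clustering.** Statistical methods (20a,b,c) says intra-cluster correlation will be accounted for but gives no ICC. With 41 women per site, the design effect is 1 + 40·ICC. For an assumed ICC of 0.01 it is 1.4 and the effective n is 82/1.4 = 58.6. For 0.02 it is 1.8 and the effective n is 45.6. Comparing two sites with two sites leaves 2 between-site degrees of freedom, with a critical t of 4.30. At d = 0.44 with a median split:
- ICC 0.01: noncentrality 0.44·√(58.6/2) = 2.38 for the score and 0.170/√[(0.250 + 0.221)/58.6] = 1.90 for the cut. Power is 28% against 20%, a gain of 8 points.
- ICC 0.02: noncentrality 2.10 and 1.67. Power is 23% against 17%, a gain of 6 points.

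If the same design effects are applied but participant-level degrees of freedom are kept, the figures are 66% against 46% and 55% against 38%. The size of the gain therefore depends heavily on how clustering is handled.

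**The case against.** The strongest reply is that the protocol nowhere says attitude or knowledge is collected as a score, or that one is cut. A reader might infer that scores will be cut to yes/no at an unstated threshold. The text does not establish this. Perceived control carries the same wording under Outcomes (12) and is then analysed by means and a t-test, so in this protocol the word proportion does not by itself fix a binary analysis. For knowledge, a proportion of level could mean the share at each of several levels, or percent correct, which is close to the score recommended here. This part of the reply stands, and the point is conditional for that reason.

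The reply also notes that the test and cut-point for a secondary outcome are commonly left to a statistical analysis plan, so their absence alone is no fault. That too stands. What remains is the outcome definition. It is the only specification the protocol gives for these two outcomes, and an analysis plan that follows it would inherit it. The perceived-control example also shows that Outcomes (12) and Statistical methods (20a,b,c) need to be brought into line.

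Finally, every effect size and ICC above is assumed, and with two sites per arm both analyses are weak. This limits the size of the benefit but does not change its direction.

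**Conclusion.** The point holds conditionally and is minor. Attitude and knowledge are defined only as proportions and have no score analysis, while the evidence on the tools and the handling of the two sister constructs make graded scores likely.

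If the scores are graded, normally distributed and compared with 82 per arm, ignoring clustering and with a central cut, the loss is about 5 to 20 points for effects of 0.4 to 0.7 SD. Over other effects and cuts it runs from about 2 points (0.8 SD, central cut) to about 37 (0.5 SD, a cut that 80% of controls exceed: 52% against 89%). With 2 between-site degrees of freedom and an ICC of 0.01 to 0.02, it is about 6 to 8 points at 0.44 SD.

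The documents therefore support neither a single unconditional loss figure nor a claim that the gain stays near 15 to 20 points once clustering is allowed for. Uptake of contraception, the main outcome, is naturally binary and is unaffected.

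**What to change.** In Outcomes (12), define attitude as the scale score and knowledge as a score, for example the number of items correct. Word perceived control as a score too, so that it agrees with Statistical methods (20a,b,c).

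In Statistical methods (20a,b,c), add a comparison of each intervention arm with control by the difference in mean score with a 95% CI. Use the linear regression already planned for intention, with the planned allowance for clustering. Keep the percentages with a positive attitude or adequate knowledge as descriptive summaries, at a cut-point fixed before data are seen. If a tool turns out to hold only a single yes/no item, say so and keep the proportion.

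The cost is wording in two sections and a registry update, with no new data, staff or participants. The small downside is that a difference in mean score is less intuitive than a percentage, which would still be reported.
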